**Methods:**

Using a pragmatic trial design, we are implementing three complementary multi-level interventions designed to improve blood pressure measurement, provide patient care management services and offer expanded provider education resources in six primary care clinics in Baltimore, Maryland. We are staggering the introduction of the interventions and will use Statistical Process Control (SPC) charting to determine if there are changes in outcomes at each clinic after implementation of each intervention. The main hypothesis is that each intervention will have an additive effect on improvements in guideline concordant care and reductions in hypertension disparities, but the combination of all three interventions will result in the greatest impact, followed by blood pressure measurement with care management support, blood pressure measurement with provider education, and blood pressure measurement only. This study also examines how organizational functioning and cultural competence affect the success of the interventions.

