#### Outcome and process measures

We are retrospectively extracting a range of process and outcome measures (already collected by the clinics) from JHCP’s EMRs (Table 5). We are collecting aggregate data at the system, clinic and provider levels. Data will be expressed as an aggregate percentage for a time period of one week, with the denominator equal to the number of patients seen in clinic by all PCPs that week and the numerator equal to the number of patients that achieved the measure as defined in Table 5. Race/ethnicity, gender, age, and presence of other chronic illnesses (diabetes, chronic kidney disease, coronary artery disease) categories will be extracted and the aggregate data will be stratified by these categories. Race/ethnicity is self-reported at the initial clinic visit.

**Table 5 T5:** Process and outcome measures used in Project ReD CHiP

**Type**	**Measure+**	**Notes and definitions**
Primary process measure	% with uncontrolled BP with medication titration in last 3 months	Uncontrolled BP ≥140/≥90 (or ≥130/≥80 if DM or chronic kidney disease); titration can be dose increase or medication change/addition
Secondary process measures	% with BP measure in EMR in last 12 months	
	% with history of pre-HTN with BP measure in last 12 months	Two clinic BPs ≥120-<140≥80-<90; not on HTN medication
	% with HTN with measure in last 6 months	Two clinic BP ≥140/≥90 OR use of a HTN medication OR ICD9 diagnosis (401.xx)
	% with HTN on a thiazide diuretic	
	% with HTN and DM on ACE-I or ARB	DM defined by ICD9 code 250.xx
	% with lipid panel performed in last 5 years^*^	May not be possible as EMR only in all clinics since March 2006
	% with BP≥135/≥85 screened for DM in last 5 years^*^	May not be possible as EMR only in all clinics since March 2006
Implementation uptake process measures	% with BP measured with OMRON	
	% of SBP and DBP measures ending in zero	
	% of eligible patients enrolled in care management	
	% completion rate for those enrolled in care management	
	Provider behavioral intention related to assessment and partnership skills	Measured at completion of the website review and at 6 months post-intervention
	Change in provider self-reported use of assessment and partnership behaviors	Measured before the website review and at 6 months post-intervention
	% of providers receiving web training at each site	Measured at 6 months post-intervention
	Provider self-reported use of HTN dashboard	Measured at 6 months post-intervention

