Primary outcome measure	% with controlled BP	Controlled BP defined as <140/<90 (or <130/<80 if DM or chronic kidney disease present)
Secondary outcome measures	% with controlled LDL	Controlled LDL defined as <130 (or <100 if DM or coronary artery disease)
	% with controlled HDL	Controlled HDL defined as >50 in women or >40 in men
	% with controlled triglycerides	Controlled triglycerides defined as <150
	% with controlled A1C	Controlled A1C defined as <7.0
	Mean SBP, DBP, LDL, HDL, triglycerides, A1C	

+Data are aggregated in one week intervals at baseline, during and after intervention roll-out for a minimum of 24 weeks.

*These measures will only be performed in clinics that have had the EMR system in place for at least 5 years.

Abbreviations: *%* percent, *BP* blood pressure, *DM* diabetes mellitus, *EMR* electronic medical record; *HTN* hypertension, *ACE-I* angiotensin converting enzyme inhibitor, *ARB* angiotensin receptor blocker, *SBP* systolic blood pressure, *DBP* diastolic blood pressure, *LDL* low density lipoprotein, *HDL* high density lipoprotein, *A1C* glycated hemoglobin.

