#### Statistical analysis plan

We will use Statistical Process Control (SPC) charting of measures over time to determine if there is a change at the system level after the implementation of the intervention and how long after implementation the change is evident [41,42]. SPC is a set of statistical methods based on the theory of variation that can be used to make sense of any process or outcome measured over time. Data will be visually inspected in a graphical display of a p-chart (for displaying proportion per time period). In this case, the x-axis will be each week of data collection (total of 24 weeks in the baseline data collection) and the y-axis will be the percent of patients seen that week with controlled blood pressure. We will distinguish normal variation from special causes (unusual changes in the pattern of data that can be assigned to a specific cause) using a range of statistically-driven tests, including: one value outside the control limits; two of three consecutive values above or below the mean and more than two standard deviations away from the mean; eight or more values falling above or below the mean; or six or more values in a row steadily increasing or decreasing (that is, showing a trend) [42].

We are also collaborating with health economists at our institution and other CPHHD centers to design and conduct a collection of cost-effectiveness analyses from health system, patient and societal perspectives, based on data from several of the ongoing interventions currently being studied by the CPHHD. We intend to capture program, patient and spillover healthcare costs, and cost offsets. The program perspective will determine the budgetary impact of implementing the interventions. Both patient and health system perspectives measure factors impacting individuals’ ability to adhere to the protocol. The success of interventions depends, in large part, on this. Additionally, interventions may have significant spillover effects, such as additional costs or cost offsets, on the healthcare system, which could impact the sustainability of the program within study sites and the likelihood of broader dissemination.

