Many of our initial challenges involved restrictions with data access and slow information technology (IT) development. Our initial approach required clinical data to be transferred from the practices’ EMR to the research team for further analysis to define eligible patients and outcome data. With this approach, we had difficulties obtaining the data we needed in a usable and timely fashion. In addition, delays in the development of the dashboard website pushed back the rollout of the provider education intervention. We eventually moved to an approach that better utilizes the strengths of the community-based practice organization, which has an extensive history of utilizing EMR data to improve clinical quality. The community-based organization became responsible for more of the data abstraction, leveraging their experience with the nuances of their system. Partnering more extensively with members of the organization’s IT department helped to speed the data retrieval and dashboard development processes. The anticipated introduction of a new EMR system across the entire organization in 2013 highlights the importance of continuing to develop these relationships throughout the duration of the project.

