Limitations of the study deserve mention. First, it is not mandatory for physicians to view the communications skills training sessions or utilize the elements on the dashboard. This may result in reduced uptake and a potential dilution of the overall effect of the provider education intervention. Additionally, the care management intervention may not be intensive enough to encourage sustained behavior change if patients do not attend all three sessions. Furthermore, in the blood pressure measurement intervention, we are making every attempt to collect high quality data, but are primarily relying on self-reports and qualitative measures to assess adherence to the blood pressure measurement protocol. This will limit the precision with which we can examine adherence. The main limitation for the organizational assessments is that some of our measures will only be collected once, so we will not know how these have changed over the course of the intervention. However, other organizational measures will be collected multiple times, for both intervention and non-intervention sites, allowing estimation of change over time and relative to an unexposed group. Lastly, in a complex healthcare delivery system, additional system-wide or practice-based quality improvement efforts may confound the results, for example, efforts to meet the ‘meaningful use of EMRs’ metrics may improve health system-patient communication. Because data will be evaluated on the system level, other unanticipated factors, in addition to unique clinic level issues, could limit the study’s ability to detect changes in our desired outcomes.

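### A 24-week p-chart baseline with no season term and no concurrent BP series lets season and common shifts be read as intervention effects, chiefly for the BP-measurement step and the system-level chart

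*Protocol article*

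**What the plan says.** The section on the statistical analysis plan describes weekly p-charts of the percentage of patients seen with controlled BP. The baseline is a "total of 24 weeks in the baseline data collection". Special causes are found by four rules: a point outside the control limits, two of three points beyond two standard deviations, eight points on one side of the mean, or six steadily rising or falling. The Table 5 footnote puts the same number differently: "Data are aggregated in one week intervals at baseline, during and after intervention roll-out for a minimum of 24 weeks".

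The level of inference also differs by place. The abstract "will use Statistical Process Control (SPC) charting to determine if there are changes in outcomes at each clinic after implementation of each intervention", while the analysis section uses the charts "to determine if there is a change at the system level after the implementation of the intervention".

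Unexposed sites appear only in the limitations paragraph of the Discussion, for some organizational measures: "for both intervention and non-intervention sites, allowing estimation of change over time and relative to an unexposed group". No such contrast is described for BP control. The same paragraph concedes that other quality improvement efforts may confound the results.

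Three facts about data and timing matter:

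- Outcomes are extracted retrospectively from the EMR, which Table 5 dates in a note on two secondary measures: "May not be possible as EMR only in all clinics since March 2006".
- The Discussion mentions "The anticipated introduction of a new EMR system across the entire organization in 2013". Table 3 places the care management and provider education roll-out in 2012–2015.
- Under Trial status, BP measurement had reached all six clinics by September 2011. Three clinics start care management six to nine months before provider education, and three start it six to nine months after.

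**The concern.** A centre line estimated from less than half a year sits wherever the season happened to be in those weeks. If BP control varies over the year, follow-up weeks drift from that line without any intervention effect, and runs and limit breaches follow. The same holds for any shift that reaches all clinics together, such as a new EMR that changes the source of the outcome data, or another initiative in the network. The planned chart has nothing to compare such a shift with.

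At stake is the attribution of a change in the primary outcome to an intervention. The BP-measurement step is most exposed, since no study clinic is without it after September 2011. The first hypothesis in Table 1 and the lowest rung of the main hypothesis both rest on that step.

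**Working it through.** **Is there a figure to reproduce?** No. The article states no power, alpha or target effect, and the 24 weeks is a choice rather than a derived number.

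**Share of a year.** 24 / 52.18 = 0.46, or about 5.5 months.

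**Data that could exist.** 1 March 2006 to 1 September 2011 is 66 months, about 287 weeks. This is an upper bound (see the objection).

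**Baseline rate.** Table 2 gives 8,493 African American and 8,483 white patients with hypertension, 16,976 in all. Weighting each site's uncontrolled percentage by its number gives 32.1% uncontrolled, so 67.9% controlled.

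**Weekly numbers (assumed).** At four visits per hypertensive patient per year, Site A gives (2,940 + 705) × 4 / 52 = 280 a week and Site E gives (331 + 650) × 4 / 52 = 75. All six sites at two to four visits give about 650 to 1,300. The visit rate is not in the documents.

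**Size of a seasonal artefact.** For a yearly cosine of half-amplitude A and two adjoining blocks of L = 24 weeks, the largest difference in block means is 2A·sin²(πL/52.18)/(πL/52.18). With πL/52.18 = 1.445 this is 2A × 0.984 / 1.445 = 1.36A. So A = 1, 2 or 3 points can give a spurious gain of up to 1.4, 2.7 or 4.1 points. This is the worst phase, with the baseline centred on the trough.

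**False favourable signals.** Simulation: binomial weekly counts, a controlled rate of 67–68%, centre line and 3-SD limits from 24 baseline weeks, 24 post weeks directly after, no intervention effect and random phase. The four rules are applied on the favourable side only, with the eight-point rule read as consecutive. The 3-SD limits, the use of baseline weeks to set them and the adjoining placement are assumptions.

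| Patients/week | No season | 1 point | 2 points | 3 points |
|---|---|---|---|---|
| 75 | 10–11% | 13% | 20% | 29% |
| 280 | 12% | 20% | 36–38% | 48% |
| 650 | 12% | 30% | 49% | 56% |
| 1,300 | 13% | 42% | 55% | 62% |

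Ranges show the spread between repeated runs.

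**What a longer baseline does for season.**

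- A 52-week baseline with a flat centre line is not enough: at 650 a week it still gives 21%, 41% and 58% for 1, 2 and 3 points.
- A 104-week baseline with one harmonic brings the rate back to about 11–13% at 75 and 280 a week.
- A 208-week baseline with one harmonic gives 10–12% at 50 to 1,300 a week.

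**What it does for a common step.** With no intervention effect and a 2-point step in all clinics at post week 8, 84% of charts signal at 650 a week with a 24-week baseline, and 86% with 208 weeks and a harmonic. At 50 and 1,300 a week the 24-week figures are 23% and 98%. A longer baseline does not help here.

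**The case against.** The strongest defence is the stagger. The abstract promises charts by clinic, and care management and provider education start on different dates and in opposite orders. An EMR switch on one date would show on six charts at once, whereas an intervention should show at each clinic's own start. Clinics not yet exposed also form a concurrent series. This stands as partial protection for those two interventions. It does not cover the system-level chart, and the analysis section describes no cross-clinic comparison. It gives no protection to the BP-measurement step once that was in place everywhere, although that step precedes the 2013 switch by more than a year, so its exposure is to season and other shifts.

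Several stronger readings are tempting but not supported:

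- A reader might infer that baseline and follow-up fall in opposite halves of the year. The Table 5 footnote makes 24 weeks a minimum and includes the roll-out period, and the timeline figure is not available.
- A reader might infer that about 287 weeks certainly exist. Roll-out was complete by September 2011 and may have begun earlier, and Table 5 allows for clinics with under five years of EMR.
- A reader might quote false-signal rates of 51%, 90% and 99% at 280 a week. Those take the worst phase and count signals in both directions, and an unfavourable signal would not be credited to an intervention.

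It can also be said that a condensed article may leave season terms and comparison series to a fuller plan, and that the Discussion already admits confounding. Silence alone would indeed be no finding. But the article does fix the baseline length and the rules, and its limitations paragraph offers no analytic remedy.

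**Conclusion.** The concern holds in a limited form. Read as written, the plan cannot separate season or a common shift from an intervention effect in the system-level chart or for the BP-measurement step. For care management and provider education the design contains a partial safeguard that the stated analysis does not use. It is not established that such shifts will be taken for effects, only that they can be.

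The size depends on three things the documents do not give: the amplitude of any season, its phase and the weekly number of patients. Under the assumptions above, the false favourable rate rises from 10–12% to between 13% and 48% at the two clinic-sized denominators. At 75 a week with a 1-point season the excess is small. At system-sized denominators it is larger. The point merits a change to the analysis; it does not invalidate the design.

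**What to change.** 1. Extend the retrospective EMR baseline to at least 104 weeks before the device roll-out where a clinic has the data, and model season with harmonic terms instead of a flat centre line. Lengthening alone is not enough.
2. For the 2013 EMR change and other common shifts, estimate effects relative to a concurrent weekly series, with a step term at the switch. For care management and provider education, use study clinics not yet exposed. Add non-participating primary care practices in the network where extractable; once all six clinics have the devices, these are the only possible comparison for the BP-measurement step. The network has over 35 practices, but that count includes specialty practices, so the usable number is unknown.
3. Reconcile the total of 24 baseline weeks in the analysis section with the minimum of 24 weeks in the Table 5 footnote, and state whether inference is by clinic, for the system, or both.

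The cost is a larger retrospective query with no patient contact. It is not free: the Discussion reports difficulty in obtaining usable and timely data. Older data may reflect different practice, and comparison clinics would not be equivalent to the study clinics. A concurrent series would also not remove initiatives confined to a single practice.

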## Methods

### Study design and specific aims

#### Specific aims

This ongoing study has three specific aims, which are reflected in Table 1 with associated hypotheses and primary outcome measures. First, we are implementing a multi-level system quality improvement intervention to reduce racial disparities in blood pressure control via three multi-level interventions designed to standardize the measurement of blood pressure, provide patient care management services, and offer expanded provider education resources.

**Table 1 T1:** Project ReD CHiP’s specific aims, hypotheses and main outcome measures

**Specific aims**	**Hypotheses**	**Process and outcome measures**
To perform a multi-method, staged quality improvement intervention (better blood pressure measurement, patient care management and provider education) to increase guideline concordant hypertension care and to reduce racial disparities in blood pressure control.	• Better blood pressure measurement and better blood pressure data will lead to less clinical inertia and, ultimately, better blood pressure control and less racial disparities.	• % of patients with controlled BP and % of patients with uncontrolled BP with medication titration in the last 3 months
	• Each intervention will have an additive effect and the use of all three interventions will result in a higher percentage of patients receiving guideline-concordant hypertension care and a greater reduction in racial disparities than any single combination or any combination of two interventions.	• % of patients with controlled BP and racial disparity in controlled BP
	• The care management intervention will have greater net improvement in blood pressure control at the clinic level than the provider education intervention. The provider education will have an additive and greater effect when implemented after the care management intervention than when employed without the care management intervention.	• % of patients with controlled BP and racial disparity in controlled BP
To determine the association of organizational functioning and organizational cultural competence with guideline concordant hypertension care and racial disparities in blood pressure control.	• Clinics will reflect their local surroundings and clinics with a higher percentage of minority persons will have lower organizational functioning.	• % of patients with BP control, stratified by race, compared across clinics

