**Clinic Characteristics**						
Primary care providers, n	9	11	11	5	3	6
Patients, n	7,755	4,733	14,887	3,681	5,628	6,161
AA patients, %	65.6	90.1	23.3	18.4	17.7	20.2
White patients, %	28.0	4.4	68.9	77.7	73.3	72.6
AA patients with HTN, n	2,940	2,777	1,493	359	331	593
AA patients with uncontrolled HTN, %	33.1	38.8	29.7	40.1	40.5	42.8
White patients with HTN, n	705	80	4,209	1,362	650	1,477
White patients with uncontrolled HTN, %	29.2	33.9	24.3	34.9	37.1	30.6

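### As written, the primary outcome counts every patient seen, so it mixes how common hypertension is with how well it is controlled

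*Protocol article*

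**What the plan says.** The Outcome and process measures section sets a weekly percentage "with the denominator equal to the number of patients seen in clinic by all PCPs that week". Its numerator counts those who meet the relevant Table 5 definition. The Statistical analysis plan section repeats this for the primary chart: "the y-axis will be the percent of patients seen that week with controlled blood pressure".

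The primary outcome row of Table 5 reads "Controlled BP defined as <140/<90 (or <130/<80 if DM or chronic kidney disease present". It gives cut-offs and no diagnosis. Other rows of the same table do name the condition, for example "with HTN on a thiazide diuretic", and one secondary process row carries a full definition of hypertension.

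Table 2 describes the clinics on a different base. Its row "AA patients with uncontrolled HTN" and the matching row for white patients give lack of control within the hypertensive group. Table 1 uses percent controlled for the racial disparity under Aim 1 and, under Aim 2, the percent "of patients with BP control, stratified by race, compared across clinics".

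**The concern.** Taken at its word, the rule places people without hypertension in the denominator and, if their reading is normal, in the numerator. Percent uncontrolled then becomes roughly hypertension prevalence times lack of control among the hypertensive. A difference between races or clinics can come from either factor, but the interventions and hypotheses are about the second.

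Table 2 implies that hypertension is more common in African American than in white patients at all six sites. The disparity outcome could therefore show a gap when control is equal, and a clinic could look good because few of its patients are hypertensive. The planned stratification by race, gender, age and other chronic illness does not include hypertension, so it does not remove the problem.

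**Working it through.** **Inputs.** All from Table 2: patients per site, percent African American (AA) and white, hypertensive (HTN) patients by race, and percent uncontrolled among them.

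**Check of the stated total.** 7,755 + 4,733 + 14,887 + 3,681 + 5,628 + 6,161 = 42,845, as the text says. HTN counts exist only for AA and white patients, so these two groups are the base: 15,738 AA + 24,095 white, about 39,834 after rounding.

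**Prevalence** = HTN count / (site size × race share). Site A, AA: 2,940 / (7,755 × 0.656) = 57.8%. Pooled: AA 8,493 / 15,738 = 54.0%; white 8,483 / 24,095 = 35.2%; together 16,976 / 39,834 = 42.6%.

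**Uncontrolled among HTN, pooled.** AA 3,026 / 8,493 = 35.6%; white 2,424 / 8,483 = 28.6%; gap 7.1 points before rounding. Both races together: 32.1%.

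**Uncontrolled among all patients** = prevalence × uncontrolled share. The base case assumes that visits mirror the panel and that no non-HTN patient exceeds the cut-off. AA 0.540 × 0.356 = 19.2%; white 0.352 × 0.286 = 10.1%; gap 9.2 points before rounding.

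**Splitting the gap.**
- Prevalence part = (0.540 − 0.352) × (0.356 + 0.286)/2 = 6.0 points (66%).
- Control part = (0.540 + 0.352)/2 × (0.356 − 0.286) = 3.1 points.
- With equal control at 32.1% in both races, the gap left is 0.321 × (0.540 − 0.352) = 6.0 points.

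**By site** (gaps from unrounded values):

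| Site | HTN prevalence AA / white, % | Gap among HTN, points | Gap among all, points | Prevalence share of the all-patient gap |
|---|---|---|---|---|
| A | 57.8 / 32.5 | 3.9 | 9.6 | 82% |
| B | 65.1 / 38.4 | 4.9 | 12.2 | 79% |
| C | 43.0 / 41.0 | 5.4 | 2.8 | 19% |
| D | 53.0 / 47.6 | 5.2 | 4.6 | 44% |
| E | 33.2 / 15.8 | 3.4 | 7.6 | 89% |
| F | 47.6 / 33.0 | 12.2 | 10.3 | 52% |

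**Sensitivity.** The article gives neither the visit mix nor the share q of non-HTN patients above the cut-off. If HTN patients are seen r times as often, the share p of HTN patients becomes rp / (rp + 1 − p). The prevalence part becomes the difference in that share × (mean uncontrolled share − q). Pooled prevalence share of the gap, with the points left under equal control in brackets:

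| r | q = 0 | q = 5% | q = 10% |
|---|---|---|---|
| 1 | 66% (6.0) | 62% (5.1) | 57% (4.1) |
| 2 | 57% (5.8) | 53% (4.9) | 48% (4.0) |
| 3 | 51% (5.1) | 47% (4.3) | 42% (3.5) |

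**Clinics, races pooled.** Control among HTN patients, A to F: 67.7, 61.3, 74.3, 64.0, 61.8, 65.9%. Among all patients: 83.8, 75.3, 89.3, 82.5, 92.7, 87.7%. Site E moves from fifth to first. Across the six sites the all-patient figure correlates −0.94 with prevalence and 0.35 with control among HTN patients. Over the sensitivity grid the first correlation lies between −0.75 and −0.94.

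**Clinics, by race (base case).** Among AA patients Site C is best on both measures (29.7% uncontrolled among HTN, 12.8% among all). Site E moves from fifth to second (13.5% among all) and Site B from third to last (25.3%). Among white patients Site E moves from last (37.1%) to first (5.8%).

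**Within-clinic charts.** A gain of 5 points among HTN patients shows as 5 × HTN share. Pooled, this is 5 × 0.426 = 2.1 points at r = 1, 5 × 0.598 = 3.0 at r = 2 and 5 × 0.690 = 3.5 at r = 3. Chart noise shrinks too: signal-to-noise relative to an HTN-only chart is √[(1 − 0.321)/(1 − 0.321 × share)], or 0.89 to 0.93, a loss of about 7% to 11%.

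**The case against.** The strongest reply is that the general denominator is shorthand. It cannot be literal for rows such as the percent of providers trained or the percent of readings ending in zero, and it fits poorly with the rows that name hypertension. The dashboard and Table 2 speak of hypertension control, and a full protocol may hold row-by-row denominators. This stands as a point about intent: the authors may well have meant hypertensive patients. It does not settle the matter, because the analysis section restates the all-patient rule specifically for blood pressure control and nothing in the article corrects it. The rule is stated, not left out.

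A second reply is that the planned analysis compares each series with its own baseline weeks. This also stands. With a stable visit mix, prevalence creates no false shift, and the loss of signal-to-noise is modest. The reply does not protect the racial gap or the comparison across clinics.

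A third is that Aim 2 asks about association with organizational functioning and cultural competence, stratified by race, and is not a ranking. That limits what the race-pooled Site E result shows. But an association across clinics is still distorted when the outcome carries prevalence with it.

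A reader might also infer that children enter as controlled, since medicine/pediatric providers are listed. The article does not say that pediatric visits are extracted, so this is not claimed.

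**Conclusion.** The point holds as a defect in the stated primary outcome: it mixes prevalence with control, against the aim and against the base used in Table 2. In the base case the pooled gap is 9.2 points instead of 7.1, and about 6.0 would persist under equal control. Across visit ratios of 1 to 3 and 0 to 10% raised readings in non-hypertensive patients, 3.5 to 6.0 points would persist, and prevalence accounts for 42% to 66% of the gap. Those ranges are assumptions, because the article gives no figures.

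Three stronger readings are tempting and not supported:
- That the gap is mostly prevalence everywhere. In the base case the share is above 75% at Sites A, B and E, but 19% at C and 44% at D, and the pooled share can fall below half.
- That Site E is best on any reading. This is so for pooled races and for white patients in the base case. Among African American patients Site C leads on both measures. With r = 3 and q = 10%, Site C also overtakes Site E for pooled races (20.7% against 21.7% uncontrolled).
- That the before/after charts are biased. They are diluted, not falsely shifted, provided the visit mix is stable.

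**What to change.** In the Outcome and process measures and Statistical analysis plan sections, and in the primary outcome row of Table 5, define the denominator of the blood pressure control percentage (overall, by race and by clinic) as patients seen that week who meet a hypertension definition. Table 5 already holds one. Apply it identically at baseline, during roll-out and afterwards, and state that it matches the base of Table 2 or explain the difference. Keep the all-patient percentage as a descriptive series only.

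Fixing each patient's hypertension status before the baseline weeks would stop new labelling from moving the series. However, it drops new patients and new diagnoses in a project that runs from 2010 to 2015. It may serve as a sensitivity analysis and is not required.

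The cost is a filter in the retrospective record extraction, a few sentences of text and smaller weekly denominators, hence wider control limits, mainly for the smaller race groups at some clinics. The extraction work is not nil: the article itself reports difficulty with data access and an expected change of record system.

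### The eight-value special-cause test does not require consecutive values, so as written it signals in every planned 24-week series

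*Protocol article*

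**What the plan says.** The Statistical analysis plan section says "Data will be visually inspected in a graphical display of a p-chart" and names four tests for telling special causes from normal variation:

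- Limits test: a single weekly point beyond the chart's limits.
- 2-of-3 test, which states a sequence: "two of three consecutive values above or below the mean and more than two standard deviations away from the mean".
- Eight-value test, which states none: "eight or more values falling above or below the mean".
- Trend test, which again states a sequence: "six or more values in a row steadily increasing or decreasing".

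On series length, the same section gives a "total of 24 weeks in the baseline data collection", and the footnote to Table 5 (Outcome and process measures) says "Data are aggregated in one week intervals at baseline, during and after intervention roll-out for a minimum of 24 weeks". On use, the Methods part of the Abstract says the charts serve "to determine if there are changes in outcomes at each clinic after implementation of each intervention". The Statistical analysis plan section adds that they should also show how long after implementation a change appears. The article describes no other analysis of effectiveness.

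**The concern.** A run test is informative because an unbroken run on one side of the centre line is rare in a stable process. Without the requirement of an unbroken run, the test only counts how many points lie on each side, and in a long enough series that count must reach eight on one side or the other.

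Two readings of the charts would be affected. The first is whether a change occurred: a test that signals in every series, baseline included, carries no information about any intervention. The second is when it occurred: in a stable process with no ties, the literal test first signals somewhere between the 8th and the 15th point counted. An apparent delay of 8 to 15 weeks after go-live would then come from the rule itself.

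**Working it through.** The article states no false-signal rate, so there is no plan figure to reproduce first.

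**Inputs from the article.** The four tests as listed; 24 baseline weeks; at least 24 weeks of data; a p-chart of weekly proportions. Table 2 gives 24.3% to 42.8% uncontrolled by site and race, so controlled proportions of 0.60 to 0.72 are plausible.

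**Assumptions, not in the article.** Control limits at 3 SD (a separate 2-SD test implies wider limits than 2 SD); independent weeks; 30 to 800 patients per week; the 2-of-3 test applied on one side; a trend counted as six points (five successive steps).

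**Step 1: the literal test, by counting.** With *n* values and none equal to the mean, the test stays silent only if at most 7 lie above and at most 7 below, so *n* ≤ 14. At *n* = 15 it must signal. Allowing ties, silence at 24 weeks needs at least 24 − 14 = 10 weekly values exactly equal to the mean.

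**Step 2: the literal test, by probability.** For a stable series with each value equally likely to fall on either side and *n* ≤ 15, P(signal) = 2 × P(Bin(*n*, 0.5) ≥ 8):

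| Weeks | P(signal) |
|---|---|
| 8 | 0.8% |
| 10 | 2 × (45 + 10 + 1)/1024 = 10.9% |
| 12 | 38.8% |
| 14 | 79.1% |
| 15 or more | 100% |

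**Step 3: the literal test on a discrete p-chart, ties allowed.** Binomial data with p = 0.65, the centre line from the series itself and 100,000 series per setting:

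| Patients per week | 15 weeks | 24 weeks |
|---|---|---|
| 50 | 96.2% | 100% |
| 100 | 97.1% | 100% |
| 400 | 98.6% | 100% |

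Ties soften the 15-week bound slightly and make no difference at the planned length.

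**Step 4: the four tests with eight *in a row*.** Chance of at least one signal in a stable 24-week window, 300,000 series:

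| Source of limits | Any of the four tests |
|---|---|
| Known limits, normal data | 19.7% |
| Known proportion, binomial data | 13.8–18.3% |
| Fixed from a 24-week baseline, applied to the next 24 weeks, normal data | 24.9% |
| The same, binomial data | 22.4–24.0% |
| Calculated from the same 24 points | 10.2–14.3% |

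With known limits and normal data, the separate rates are 6.3% (outside limits), 4.3% (2-of-3), 6.9% (run of eight) and 4.5% (trend). As a check on the first, 1 − (1 − 0.0027)^24 = 6.3%.

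Counting a trend as six successive steps lowers 19.7% to 16.6% and 24.9% to 21.9%. With normal data and limits from the same 24 points, it gives 6.6–10.9%.

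Adding the sequence requirement thus takes the run test from 100% to about 7% per 24 weeks with known limits, or 10.7% with limits fixed from baseline (normal data).

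**The case against.** **Probably a slip.** The test stands in a condensed list, between two sequential tests and with a methods citation. The stated aim is to detect unusual patterns, which a plain count cannot do. Nothing shows that the team would run the charts on the literal reading. This stands, and it limits the point to a correction of the text. It does not remove the point, because the article states the rule and a reader can apply only what is stated.

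**The 15-week bound is not exact.** This is right when a weekly value can equal the mean (96–99% in step 3), and it does not matter at 24 weeks.

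**Stronger readings that the document does not support.**

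- A reader might infer that false findings are nearly certain even after correction: 6 clinics × 3 interventions = 18 windows, and 1 − (1 − 0.20)^18 = 98%. This treats the windows as independent and any single signal as proof. The article states no such decision rule. It also refers to change at the system level, and its staggered roll-out, with the order reversed in three clinics, lets timing and replication inform the reading.
- A reader might infer that p-chart limits are too narrow because patients and providers recur from week to week. The article gives neither weekly denominators nor extra-binomial variation, so any figure for this would be invented.
- A reader might count as gaps the direction of signals, the construction of limits or the lack of effect estimates. An article may leave these to the full plan.
- Dropping two of the four tests is a preference. It gives about 13% per window with known limits but 17–18% with limits estimated from baseline.

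**Conclusion.** The eight-value test is wrong as written. At the planned 24 weeks it signals in essentially every stable series, before or after an intervention, and so cannot do what the section asks of it. This follows from counting and needs no assumption beyond fewer than ten of the 24 values being tied with the mean.

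The false-signal rate of the corrected set is a note on interpretation only. It contradicts no figure in the article, which sets no tolerance for it. The rate is roughly 10–25% per stable 24-week chart with 3-SD limits, independent weeks and a six-point trend: about 20% with known limits (normal data), 22–25% with limits fixed from a 24-week baseline, and 10–14% with limits from the same 24 points. It supports caution about an isolated signal on one clinic's chart, and nothing stronger.

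**What to change.** Restate the test as: *eight or more consecutive values on the same side of the mean*. Add one sentence saying that only signals arising after an intervention's go-live count as evidence for that intervention.

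In reporting, it would help to state how the limits were set and to say that an isolated signal on a single clinic's chart is not by itself taken as an intervention effect.

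The cost is one phrase and one sentence. No change to data collection, chart type or the other three tests is needed.
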